### Randomisation and blinding

As this is not a homogenous group, prior to randomisation, participants will be stratified according to intensity of their cancer treatment regimen: high intensity versus low/moderate intensity treatment. Table 2 demonstrates stratification of the most common cancers diagnosed in the AYA age range. Any participant recruited with a diagnosis not listed in Table 2 will be discussed within the research team and treating clinicians to determine the intensity of their treatment regimen. The division between low/moderate versus high intensity relates to the likelihood of low blood counts and degree of immunosuppression from the treatment regimen.

**Table 2 Tab2:** Stratification strategy of most common adolescent and young adult cancer diagnoses based on treatment regimen

Low/moderate intensity treatment diagnoses	High intensity treatment diagnoses
Hodgkin lymphoma	Acute lymphoblastic leukaemia
Germ cell tumours	Lymphoblastic lymphoma
Gynaecological tumours	Burkitt lymphoma
Non-Hodgkin lymphoma (excluding Burkitt)	Soft tissue and bone sarcoma
Melanoma	Squamous cell carcinoma of the head and neck

Following stratification, participants will be randomised via a computer-generated block randomisation (sealed envelope) procedure. The allocation sequence will be generated and maintained by a member of the research team that is not involved in patient contact or treatment. Both high and moderate intensity treatment groups will be randomised in block sizes of 4 and 8 into the two intervention groups: immediate exercise or usual care (delayed exercise) intervention. The block randomisation will allow for equal groups to be created by the end of the recruitment. Given the nature of the intervention, it is not possible to blind the investigators or the participants to their group allocation. However, the study personnel responsible for conducting primary outcome assessments will be blinded to participant group allocation.

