#### Patient-reported treatment-related toxicities

In order to determine that participants meet the safety requirements to complete exercise sessions, they will be required to undergo weekly full blood count (FBC), urea and electrolyte (U&E) and liver function (LFT) blood tests. These results will be reviewed prior to each exercise session to ensure participants meet predetermined safety parameters for exercise [30]. The results will also be reviewed and graded as per the Common Terminology Criteria for Adverse Events (CTCAE Version 5.0) [42] to determine any impact exercise may have on these variables. Further, participants will be contacted weekly by a member of the research team blinded to group allocation to determine if the participant has experienced any additional treatment-related side effects, including but not limited to nausea, vomiting, constipation, pain and fatigue (Additional file 1) [42]. These participant-reported side effects will also be graded by the research team as per the CTCAE version 5.0 [42].

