## Discussion

To the best of our knowledge this will be the first RCT to examine the benefits of a structured, supervised exercise intervention in AYAs from their cancer diagnosis and throughout their subsequent treatment. Furthermore, it will be the first RCT to explore the potential impact that exercise has on patient-reported treatment-related toxicities. In addition, we will explore any relationship evident between changes in physical functioning and patient-reported treatment-related toxicities.

The design of this study represents both a strength and potential weakness. While a control group is essential to be able to determine any impact that exercise has in the intervention group, the research team deems it unethical to actively encourage sedentary behaviour. In order to address this, the cross over design allows for both groups to be exposed to the exercise intervention and will determine the most appropriate timing for the intervention. Additionally, both groups will be asked to record any physical activity they complete throughout the trial which will be accounted for as potential covariate in the final analysis. Nonetheless, the crossover design will also permit an ability to evaluate any changes in exercise-related beliefs or practices in the immediate exercise group, following their initial 10-week exercise programme.

If it is demonstrated that this exercise intervention prevents functional decline associated with cancer treatment in AYAs, then such programmes can be adopted widely in this cohort. Further, this research will allow clinicians to better understand the potential benefits of exercise on mitigating treatment-related toxicities encouraging targeted research by toxicity, aiming to improve overall treatment tolerance in AYAs.

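### The weekly symptom part of the toxicity outcome is limited to treatment-related side effects in an open-label exercise trial, so it is open to attribution that differs between arms

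*Protocol article*

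**What the plan says.** All places are in the protocol article.

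- **Symptoms** (Patient-reported treatment-related toxicities). The contact is blinded: "participants will be contacted weekly by a member of the research team blinded to group allocation". Its purpose is "to determine if the participant has experienced any additional treatment-related side effects, including but not limited to nausea, vomiting, constipation, pain and fatigue". The article points here to Additional file 1. Grading follows: "These participant-reported side effects will also be graded by the research team as per the CTCAE version 5.0". The article does not say who decides that a symptom is treatment-related, or what happens to one that could come from exercise.
- **Blood results** (same section). Weekly blood counts, electrolytes and liver function tests form the other part of the outcome: "The results will also be reviewed and graded as per the Common Terminology Criteria for Adverse Events (CTCAE Version 5.0". No relatedness condition is attached.
- **Blinding** (Randomisation and blinding). The article says "it is not possible to blind the investigators or the participants to their group allocation". Assessor blinding is stated there for the primary outcome; the section on toxicities adds the blinded caller.
- **Use of the outcome.** The Background lists the effect of the intervention on treatment-related toxicities among the secondary aims. The Discussion claims novelty for it: "it will be the first RCT to explore the potential impact that exercise has on patient-reported treatment-related toxicities".

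**The concern.** The outcome is meant to test exercise, yet its symptom part is defined by cause, and exercise is a competing cause of two of the named symptoms. The Exercise prescription section sets resistance work at 60–80% of one-repetition maximum and encourages further aerobic exercise outside sessions, so soreness and tiredness from training are plausible. A participant who knows they are training may put tired legs down to the gym and not mention them when asked about effects of treatment. A usual-care participant with the same symptom has less reason to do so. The recorded rates would then differ with no difference in tolerance of cancer treatment.

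Because the arms swap at 10 weeks, the filter would follow whichever group is exercising. The crossover does not cancel it.

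At stake is a secondary aim that the article presents as a first for a randomised trial. The primary outcome is untouched.

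**Working it through.** The plan states no figure on this point, so there is nothing to reproduce. The check has two parts.

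**1. Does anything in the article remove the filter or recover what it loses?**

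- *Blinded caller.* This protects against the caller's expectations. It does not act on an answer given by someone who knows their arm and has been asked about effects of treatment. A caller who tried to separate the causes would have to ask about training, which puts the blind at risk.
- *CTCAE grading by the research team.* This grades the severity of what is reported. It cannot restore what was not reported.
- *Questionnaires* (Patient-reported activity and quality of life). Fatigue is also measured by EORTC QLQ-C30 and a multidimensional fatigue scale, with no attribution filter stated. Per the Abstract, assessments are at 0, 10 and 20 weeks, so these do not replace weekly grades.
- *Adverse event monitoring* (Feasibility). This covers assessments and supervised sessions. A symptom felt at home and put down to training is not clearly captured.
- *Meaning of treatment.* If it included the exercise programme, the filter would disappear. The Background ties fatigue and pain to cancer treatment regimens, and the Discussion speaks of exercise mitigating these toxicities, so cancer treatment is the natural reading.

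**2. How large could the effect be?** Illustration only. Let p be the true risk of a recorded symptom, equal in both arms, and q the share of exercisers' symptoms put down to training and not recorded. Neither value is in the document. Then:

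- observed exercise risk = p(1 − q)
- risk ratio = p(1 − q)/p = 1 − q
- risk difference = −pq

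The planned total of 40 gives about 20 per arm. The last column is the normal-approximation chance that a two-sided 5% comparison of two proportions falsely favours exercise; without bias it is nominally 2.5% in that direction.

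| p | q | observed exercise risk | risk ratio | risk difference | chance of a false result for exercise |
|---|---|---|---|---|---|
| 0.4 | 0.1 | 0.36 | 0.9 | −0.04 | 4% |
| 0.4 | 0.3 | 0.28 | 0.7 | −0.12 | 12% |
| 0.6 | 0.1 | 0.54 | 0.9 | −0.06 | 6% |
| 0.6 | 0.2 | 0.48 | 0.8 | −0.12 | 11% |
| 0.6 | 0.3 | 0.42 | 0.7 | −0.18 | 20% |
| 0.6 | 0.5 | 0.30 | 0.5 | −0.30 | 48% |
| 0.8 | 0.5 | 0.40 | 0.5 | −0.40 | 75% |

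For p = 0.6, q = 0.3: the pooled risk is (0.60 + 0.42)/2 = 0.51. The null standard error is √(0.51 × 0.49 × 2/20) = 0.158. The alternative standard error is √(0.60 × 0.40/20 + 0.42 × 0.58/20) = 0.155. Then Φ((0.18 − 1.96 × 0.158)/0.155) ≈ 0.20.

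Recording symptoms whatever their cause sets q = 0, which returns a risk ratio of 1 and a risk difference of 0 when there is no true effect.

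**The case against.** The strongest reply is that the deciding instrument is not visible. If Additional file 1 is a checklist that asks about each symptom regardless of cause, there is no filter in practice. That stands as a limit: it cannot be said as fact that exercisers' symptoms are lost. It does not remove the point, because the article's own outcome wording is by cause and would then need to match the form.

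The direction is also not established. Supervised participants see staff twice a week and might report more. Usual-care participants may exercise too and keep activity journals, so they can have a rival explanation as well. This stands: bias towards exercise is plausible, not certain. The illustration assumes its own inputs and shows only that the effect could matter.

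Any-cause grading does change the quantity measured, since the stated aim is treatment-related toxicity. Keeping attribution as a secondary summary preserves that view.

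Three stronger readings are tempting and are not supported:

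- *The whole toxicity outcome is filtered.* It is not; the graded blood results have no relatedness condition.
- *Unblinded participants judge relatedness.* The text does not say who judges. That participants filter their answers is an inference from how the contact is described.
- *Usual care goes unsampled for bloods in weeks 0–10, so low counts are found more often in exercisers.* The stated purpose, "In order to determine that participants meet the safety requirements to complete exercise sessions, they will be required to undergo weekly full blood count", invites this, since usual care has no sessions then. But the sentence is not limited to one arm, and grading the results to judge the impact of exercise implies data from both.

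**Conclusion.** The point holds for the participant-reported symptom component only. Its wording restricts it by cause, participants are unblinded, exercise is a plausible rival cause of pain and fatigue, and no measure described in the article clearly prevents or recovers differential attribution. The likely direction favours exercise, without certainty.

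The size depends wholly on q, which the document does not give. Over assumed ranges of p from 0.4 to 0.8 and q from 0.1 to 0.5, the spurious risk difference runs from −0.04 to −0.40. This rests on equal true risk in both arms, on losses only among exercisers, and on Additional file 1 not already asking about symptoms irrespective of cause. It is worth correcting because the change is small and the outcome supports a headline claim of the trial.

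**What to change.** In the section on patient-reported treatment-related toxicities, and in Additional file 1 if it does not already do so:

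1. Ask about each listed symptom at every weekly contact, whatever its cause, and grade it by CTCAE.
2. Define the comparison between arms on these any-cause grades.
3. Record attribution as a separate item, report it as a secondary summary, and do not use it to decide what counts.

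The cost is a change of wording in the outcome definition and possibly in the call form, with no added visits. Any-cause grades will include some training soreness, so the estimate may be slightly less favourable to exercise; the attribution summary lets readers see how much. For weeks already collected under a different question, the report should say which wording applied.

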#### Feasibility

The feasibility of the exercise intervention will be determined based on eligibility rate, recruitment rate, compliance to the study protocol, adherence to the exercise intervention and withdrawal rates. Safety will be assessed by monitoring for any adverse or serious adverse events during any of the assessments or supervised exercise sessions. The research team includes a senior and experienced cancer clinician who will provide guidance on individual safety concerns throughout the study. Regular meetings with the research team will be held to review protocol adherence and safety reports. Any adverse events will be reported to the appropriate HREC bodies within an expedient time frame. If in the event of frequent adverse events occurring, which are deemed a result of the intervention, then a collaborative decision can be made to cease the trial. All data will be collected, input and stored in accordance with HREC guidelines as outlined in FiGHTINGF!T Protocol Version 2 03012019. Any modifications to the protocol will be submitted and approved to the relevant HREC bodies and disseminated as appropriate.

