### Intervention

All participants will complete baseline assessments and be randomised prior to commencing (± 2 weeks) systemic treatment. All exercise programmes will be individually prescribed by an Accredited Exercise Physiologist (AEP) and tailored relative to each patient’s presentation. The programmes will follow the American College of Sports Medicine (ACSM) and Exercise and Sports Science Australia (ESSA) guidelines for combined aerobic and resistance exercise for cancer patients [16, 21]. All exercise sessions will be undertaken in a one-on-one basis within a purpose-built gymnasium in the hospital setting and will be supervised by an AEP. No concomitant care or therapies will be specifically permitted (or prohibited) during the trial. However, it is anticipated that participants may exercise outside of the trial, and therefore, all participants will be asked to complete an activity journal to capture any incidental exercise they may perform. The contents of the journal will be checked on a weekly basis by members of the research team. This weekly monitoring will also ensure participants are adhering to the study protocol and associated invention requirements.

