#### Immediate exercise group

These participants will commence their exercise programme the week following their baseline assessment and will be required to attend two supervised exercise sessions per week for 10 weeks. Sessions will be approximately 60 min in duration and scheduled at appropriate times relative to participants’ treatment schedules, with exercise conducted prior to or > 24 h following chemotherapy administration. This scheduling strategy is aimed to maintain participant safety, as well as to reduce the burden of additional appointments and limit inconvenience to the participant. Participants will complete a post-intervention assessment at 10 weeks. Following the 10-week interim assessment, participants will then receive no further structured supervised exercise intervention for the remaining 10 weeks, prior to the subsequent final assessment at 20 weeks.

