#### Exercise prescription

All exercise sessions will be multi-modal and follow the same format throughout the 10-week intervention. Participants will commence each session with a 5-min warm up, followed by aerobic bouts, a resistance training component and concluding with a 5-min cool down and static stretching period of major muscle groups. The aerobic component of the programme will be based on the participant’s physical capabilities and preference of the modalities available within the gym (including cycling on an upright/recumbent bike, treadmill walking/jogging and/or skipping) and aim to accumulate 20–30 min at moderate intensity over the duration of the session. Intensity will be monitored using heart rate (HR) and rating of perceived exertion (RPE) [28]. Moderate intensity aerobic exercise is considered 60–85% of maximal heart rate (220 − age) [29] or an RPE of 12–14. Participants who are unable to complete 20 min continuously will aim to accumulate the required load in bouts of 5 to 10 min as tolerated. The resistance training component will comprise of 6–8 exercises targeting the major muscle groups of the body. Participants will complete 2–4 sets of 8–15 repetitions, at 60–80% of 1 repetition maximum (1RM) or an RPE of 12–14 [29]. Based on the thorough baseline assessment, any pre-existing injuries or treatment-related effects will be considered when prescribing and progressing all exercises. The sessions will aim to increase in exercise intensity as tolerated. Participants will also be encouraged to engage in aerobic exercise outside of supervised exercise sessions and asked to document their activity in exercise journals to meet exercise recommendations for cancer survivors [16, 21]. Exercise programmes will be modified on a weekly basis as required relative to participants’ treatment schedules and related side effects, as well as changes in their individual physical conditioning throughout the programme. Participants’ vital signs and most recent full blood picture will be reviewed prior to commencing each and every exercise session, to determine their safety for exercise and any need for programme modification as per published guidelines [30]. In the unlikely event any injuries occur during exercise sessions, these will be documented accordingly, and participants will be offered appropriate medical treatment/care without any cost to them.

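### The safety assessment covers adverse events only at assessments and supervised sessions, so unsupervised or delayed harm is not clearly captured and usual-care periods have no comparable window

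*Protocol article*

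**What the plan says.** The Feasibility section defines how safety is judged: "Safety will be assessed by monitoring for any adverse or serious adverse events during any of the assessments or supervised exercise sessions". It then allows the trial to be ceased on the strength of such events: "If in the event of frequent adverse events occurring, which are deemed a result of the intervention, then a collaborative decision can be made".

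The Exercise prescription section takes the same line on injuries: "In the unlikely event any injuries occur during exercise sessions, these will be documented accordingly". The same section makes exercise outside the gym part of the programme: "Participants will also be encouraged to engage in aerobic exercise outside of supervised exercise sessions". Participants log this activity in a journal. Of the journal, the Intervention section says: "The contents of the journal will be checked on a weekly basis by members of the research team". Its stated purposes are to capture incidental exercise and to monitor adherence. No adverse-event question is mentioned.

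A second stream of data appears under Patient-reported treatment-related toxicities: "participants will be contacted weekly by a member of the research team blinded to group allocation". The contact asks about treatment-related side effects from an open list that includes pain and fatigue, and the answers are graded by CTCAE version 5.0. It is not restricted to one arm or one period. The Feasibility section does not mention it as a source for the safety assessment.

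**The concern.** The safety sentence is a stated rule, not a detail left out. Applied as written, it has three effects.

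- **Unsupervised exercise.** The intervention includes encouraged exercise at home, but an event during that exercise is outside the window.
- **Delayed events.** An injury that shows itself after the session, or an admission the next day, did not occur during a session.
- **Unequal observation.** Usual-care periods contain no supervised sessions, so the window is open there only at the assessment.

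At stake is what the trial can say about safety in young people on systemic cancer treatment, many of whom will have events for reasons unrelated to exercise. A table of in-window counts by condition would mislead in two ways. It would weigh against exercise, because exercise periods are watched far more often. It would also omit exercise-related events that arise outside the gym. The clause on ceasing the trial needs a judgement that events result from the intervention, and a comparable usual-care count would help that judgement.

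**Working it through.** The plan gives no numerical safety target, so there is no figure to reproduce. The check counts observation under the stated definition and then compares what each data stream covers.

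**Inputs**

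- Sessions (Immediate exercise group): participants are "required to attend two supervised exercise sessions per week for 10 weeks", at about 60 minutes each. The delayed group receives the same programme in weeks 10 to 20.
- Usual-care periods: weeks 0 to 10 in the delayed group and weeks 10 to 20 in the immediate group, with no supervised sessions in either.
- Assessments: weeks 0, 10 and 20. Week 0 precedes randomisation, so each 10-week period ends with one assessment.
- Assessment length: not given in the article. I assume 1 to 3 hours.

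**Occasions in the window, per participant per 10-week period**

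- Exercise: 2 × 10 + 1 = 21.
- Usual care: 0 + 1 = 1.

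**Hours in the window**

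- Exercise: 2 × 1 h × 10 = 20 h, plus 1 to 3 h, gives 21 to 23 h.
- Usual care: 1 to 3 h.
- Ratio: 21/1 = 21 with a 1-hour assessment; 22/2 = 11 with 2 hours; 23/3 = 7.7 with 3 hours.

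Under this definition an exercise period is therefore observed about 8 to 21 times as long as a usual-care period. The count of occasions (21 against 1) needs no assumption.

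**What each stream covers**

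| Event | Safety assessment (Feasibility) | Injury record (Exercise prescription) | Weekly blinded contact |
|---|---|---|---|
| Injury in a session | Yes | Yes | Possibly, if reported as pain |
| Injury or fall in unsupervised exercise | No | No | Not clearly |
| Harm first evident after a session | No | Not clearly | Not clearly |
| Unplanned admission during usual care | No | No | Only if seen as a treatment side effect |
| Treatment-related toxicity, either condition | Only if it occurs in the window | No | Yes, about 10 contacts per period |

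The last row shows that treatment-related toxicities do have a usual-care rate. The middle three rows are the gap. Weekly blood tests are also graded by CTCAE, but they are introduced as a check before exercise sessions. The article does not make clear whether they continue in usual-care periods.

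**The case against.** The strongest reply is that the article already has a broader system. A blinded caller contacts participants every week, in both conditions, with an open list and standard grading. Vital signs and blood results are reviewed before every session, journals are checked weekly, and a senior clinician advises on safety throughout. Adverse events go to the ethics committees with no session limit stated. A decision that an event results from the intervention is a causality judgement on individual cases and does not strictly need a control rate. The content of the weekly contact is in an additional file, the schedule table is not reproduced, and the full protocol (Version 2) is not shown. Any of these may already ask about injuries or admissions.

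Much of this stands, and it rules out three stronger readings that a reader might infer.

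- **That adverse events are counted nowhere else.** The weekly contact grades side effects outside sessions and could pick up some delayed harm, such as pain.
- **That nothing is known about event rates in usual-care periods.** Treatment-related toxicities are recorded there too and can be compared between arms.
- **That nearly all harm is missed, because sessions fill only 20 of the 1,680 hours (10 × 7 × 24) in a period, about 1.2%.** That is a share of clock time. It measures neither exercise exposure nor risk, which is concentrated when people exercise.

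The reply does not remove the published sentence. Reporting to ethics committees concerns events once known, not how they are found. Neither the pre-session checks nor the journal review is described as event collection. If Version 2 is broader, the article misstates it and the sentence still needs correcting.

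The gain is also limited by size. With 20 participants in an arm and no events seen, the one-sided 95% upper limit on risk is 1 − 0.05^(1/20) = 13.9%. Complete collection would not make this a definitive safety comparison, but it would make the counts interpretable.

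**Conclusion.** The point holds in a limited form. The stated safety definition leaves injuries, falls and unplanned admissions arising in unsupervised exercise or after a session without clear capture. It also gives exercise periods 21 observation occasions against 1 in usual care, or about 8 to 21 times the hours if an assessment lasts 1 to 3 hours. Adverse and serious adverse event counts under that definition are therefore not comparable between conditions. Treatment-related toxicities are comparable, through the weekly contact, but the plan does not connect them to the safety assessment.

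The number of events that would be missed cannot be estimated from the article. The conclusion assumes that the weekly contact is limited to treatment-related side effects, as its wording indicates. The primary outcome is unaffected. This should be changed because it is cheap and concerns a stated safety outcome.

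**What to change.** 1. Redefine the safety outcome as all adverse and serious adverse events from baseline to week 20 in both arms, wherever they occur.
2. Add one neutral question to the existing weekly contact, asking about any injury, fall or unplanned admission since the last contact. It should not mention exercise or sessions, so that the answer is less likely to reveal the allocation to the caller. Check first whether the form in the additional file already asks this.
3. Report events by randomised arm and by period (weeks 0 to 10 and 10 to 20), with events during sessions and assessments as a subset.
4. State that the weekly CTCAE toxicity data feed the safety review alongside these events, and bring the injury sentence under Exercise prescription into line with the new definition.

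The team's process for deciding whether to cease the trial need not change; it would simply see both arms' events. If the full protocol already collects events this way, correcting the article's sentence is enough.

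The cost is a minor amendment and some extra event forms, with no added visits or staff. The downside is a small risk that a participant describing an injury unblinds the caller.
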